## Procedure

In this randomized controlled trial, each participant will be randomly assigned (1:1:1) to receive either a comic book (Intervention 1, 15 min long) a flyer (Intervention 2, 15 min long), or no intervention (Control). The randomization process will be stratified for the age category (i.e., 10–14 years; 15–19; 20–24) to ensure that within each category, a similar number is allocated to each arm (see Fig. 1). The allocation sequence will be generated by colleagues at the Technical University of Munich, who are not further involved in the conduct of the trial. They will use statistical computing software to define a random allocation sequence for all potentially eligible participants included in the pre-defined sample roster.

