**Fig. 1 Fig1:**
[figure not shown]
Trial flow chart

As part of the DASH cohort study, which this trial is nested, all participants will take part in a survey interview of approximately 60–90 min. Each interview will begin with the data collector providing the consent form. If the participant consents, they will be asked survey questions regarding mental health literacy, anxiety, and depression before the intervention is administered, which will serve as baseline measures. For participants assigned to the comic book intervention, the data collector will provide the printed comic book to the participants, reading the text aloud. For participants assigned to the flyer intervention, the process will be the same where the data collector will provide the printed flyer, reading the text out loud. Participants in the control group will be provided with no additional instructions or interventions. Participants will then be asked other survey questions regarding sexual and reproductive health providing a brief break between the intervention implementation and the post-intervention survey. All participants will be surveyed on mental health literacy, anxiety, depression, and intentions to cope as a post measure.

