## Data analysis

We will assess participants’ sociodemographic characteristics, including age, gender, education levels, ethnicity, religion, household characteristics, and their parents’ highest level of education and occupation with outcome measures. To assess the effectiveness of an intervention on mental health literacy (MHL), we will build a multiple regression model. We will also assess each sub-scale component of MHL (knowledge about mental health, knowledge about mental health, help-seeking, and stigma). Here, the independent variable is “3 arms”, representing different intervention groups, and the outcome will be “MHL after the intervention.” We will control for baseline MHL scores by including them as a covariate, following the recommendation by Senn (2006) to adjust for potential baseline differences [36]. For the analysis, we will employ dummy coding for the three trial arms to compare each intervention arm against the control arm. In addition, covariates such as depressive and anxiety symptoms, intentions to cope, age, gender, and education levels will be included in the model. Secondary outcomes will be examined using three separate linear regression models, with the trial arm” treated as a factor and the control arm serving as the reference category for each secondary outcome. To ensure the validity of our multiple regression analysis, we will calculate variance inflation factor values to check for multicollinearity among the independent variables. We will conduct statistical analyses using *R version 4.1.0* (www.r-project.org).

The final cleaned, de-identified and locked dataset of the trial will be accessible by the DASH network partners. Public access to the data will be made available upon review of the request and approval by each institute’s Principal Investigators.

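### The secondary-outcome models name only trial arm, giving up precision that the collected PHQ-2 and GAD-2 baselines, and to a small extent the age stratum, would provide

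*Protocol article*

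**What the plan says.** The Data analysis section of the Protocol article describes two kinds of model in one paragraph.

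- **MHL (primary).** "We will control for baseline MHL scores by including them as a covariate", with a cited reason for doing so. Further terms follow: "covariates such as depressive and anxiety symptoms, intentions to cope, age, gender, and education levels will be included in the model". The singular noun, and its position before the secondary outcomes are mentioned, tie this list to the MHL model.
- **Depression, anxiety, intentions to cope (secondary).** "Secondary outcomes will be examined using three separate linear regression models". Trial arm enters as a factor with control as reference. No other term is named.

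The Procedure section supplies two further facts. "The randomization process will be stratified for the age category", with three categories. After consent, in the interview described below Fig. 1, "they will be asked survey questions regarding mental health literacy, anxiety, and depression before the intervention is administered, which will serve as baseline measures". Intentions to cope is absent from that baseline list and appears only afterwards: "All participants will be surveyed on mental health literacy, anxiety, depression, and intentions to cope as a post measure".

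**The concern.** The reason for adjusting MHL for its own baseline applies equally to PHQ-2 and GAD-2. Both are measured before and after the intervention, and the article itself calls the earlier scores baseline measures. Nothing in the stated secondary models uses them for their own outcome. Age defines the randomisation strata and is a covariate for MHL, but it is not named for the secondary outcomes.

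What is at stake is precision. An arm-only comparison leaves chance baseline differences in the estimate and gives wider intervals. The Introduction says the trial will look in an exploratory way at whether the material affects anxiety and depression, since some readers of such information are affected negatively. Narrower intervals would make that exploration more informative.

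**Working it through.** **Inputs from the article (Sample size and power considerations; Table 1).** 669 per arm at wave 1; 10% attrition at wave 2, so 669 × 0.9 = 602.1 per arm; power 0.80; t-tests of means without covariates; α = 1 − 0.95^(1/√h). The minimum detectable effect (MDE) is stated to cover primary and secondary outcomes. Table 1 gives 0.17 and 0.18 for the full sample, and 0.32 and 0.34 for age subgroups.

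**Inputs not in the article.** The value of h, whether the test is two-sided (assumed so), the pre-post correlation ρ, and the share of outcome variance R² explained by age category.

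**Step 1: reproduce Table 1.** MDE = (z for two-sided α + z for 80% power) × √(2/n). With h = 6, α = 0.0207:
- n = 669: 0.1725, against 0.17 stated.
- n = 602.1: 0.1818, against 0.18 stated.

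The noncentral t calculation gives 0.173 and 0.182 for these. For the subgroups, with h = 18 (α = 0.0120), it gives 0.319 and 0.336, against 0.32 and 0.34. All four entries are matched, but h is inferred; 4 or 5 also rounds to the full-sample figures. Table 1 is thus consistent with an unadjusted comparison.

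**Step 2: add the outcome's own baseline (PHQ-2 and GAD-2 only).** The standard error (SE) is multiplied by √(1 − ρ²), and the MDE with it. An unadjusted analysis of 669 per arm is then as precise as an adjusted analysis of 669 × (1 − ρ²) per arm. Wave 1, h = 6, effects in units of the unadjusted SD:

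| Assumed ρ | SE ratio | MDE | Equivalent n per arm | Power at d = 0.17 | Power at d = 0.10 |
|---|---|---|---|---|---|
| no adjustment | 1.000 | 0.1725 | 669 | 0.787 | 0.314 |
| 0.3 | 0.954 | 0.1645 | 609 | 0.828 | 0.346 |
| 0.5 | 0.866 | 0.1494 | 502 | 0.899 | 0.420 |
| 0.7 | 0.714 | 0.1232 | 341 | 0.979 | 0.598 |
| 0.8 | 0.600 | 0.1035 | 241 | 0.998 | 0.769 |

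The SE falls by about 5%, 13%, 29% and 40%. Leaving the baseline out is equivalent to discarding 9%, 25%, 49% and 64% of the sample. These proportions do not depend on h.

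**Step 3: age stratum alone.** The SE is multiplied by √(1 − R²). For assumed R² of 0.01, 0.03 and 0.05 the ratios are 0.995, 0.985 and 0.975, a fall of about 0.5% to 2.5%. The MDE moves from 0.1725 to 0.1716, 0.1699 and 0.1681.

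**Step 4: simulation.** Three arms of 669, stratified by age with R² = 0.03, were analysed by arm only and by arm plus baseline plus stratum. The SE ratios were 0.946, 0.862, 0.712 and 0.599 at ρ = 0.3, 0.5, 0.7 and 0.8, close to Step 2, so almost all the gain comes from the baseline score. Type I error stayed near 5% in both models.

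**The case against.** The strongest reply is that silence is not exclusion. The article does not call the secondary models unadjusted; the sentence may only explain how arm is coded. A condensed article can leave covariates to a fuller plan, and calling the early scores baseline measures fits an intention to use them. This stands as a limit on confidence: a reader might infer that adjustment has been ruled out, and the text does not go that far. It does not remove the point. The article gives the model form, the factor and the reference level for these outcomes, directly after listing covariates for MHL alone.

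Other stronger readings are also unsupported:

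- **That the results would be biased or the tests invalid.** Randomisation protects the arm-only comparison, and the simulation agrees. Nor is Table 1 contradicted: an arm-only analysis gives the precision it assumes.
- **That the trial must exclude a small harmful shift.** The Introduction announces an exploration and sets no harm margin or non-inferiority aim.
- **That the gain is certainly large.** Every ρ is assumed. At 0.9 the sample multiplier would be 1/(1 − 0.81) = 5.3, but that is an optimistic value for two-item scales. At 0.3 the gain is modest.
- **That all three outcomes gain alike.** Intentions to cope has no listed pre-intervention score, so the table in the working does not apply to it.
- **That the missing age term is a serious fault.** Its omission makes the reported standard error only slightly too large.

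**Conclusion.** The point holds as one of efficiency, with moderate confidence because the article does not expressly exclude covariates. The PHQ-2 and GAD-2 models, as stated, leave unused a baseline score that the trial collects. Under ρ between 0.3 and 0.8 this costs about 5% to 40% of the standard error at wave 1. A substantial wave 1 correlation is plausible because both measurements fall within one interview of 60 to 90 minutes, but that is a judgement and not a figure from the article. A year later the correlation, and so the gain, is likely to be lower. The age stratum is a minor addition that brings the analysis into line with the randomisation. The calculation assumes a linear relation between baseline and post scores with a common slope across arms.

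**What to change.** State the secondary models in full before the outcome data are analysed:

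- Post PHQ-2 on arm + baseline PHQ-2 + age stratum.
- Post GAD-2 on arm + baseline GAD-2 + age stratum.
- Post intentions to cope on arm + age stratum. Baseline MHL, PHQ-2 and GAD-2 may be added, but no benefit has been calculated for them.

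Use the same terms at wave 2, with the wave 1 pre-intervention scores as baseline. If a fuller plan already adjusts in this way, one clarifying sentence in the Data analysis section is enough. The change is to wording only: no new data, visits or participants. Fixing the model in advance also prevents a later choice between adjusted and unadjusted estimates once results are known.

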## Discussion

This study will contribute valuable information on light-touch interventions for improving mental health outcomes for adolescents and youth in LMICs. We will use an efficient, low cost, scalable, and validated intervention to enhance MHL among adolescents and youth in Burkina Faso. Our findings will add knowledge on the effectiveness of using a comic book to increase knowledge about mental health and mental disorders, facilitate help-seeking behaviors, reduce stigma, and thereby enhance overall MHL. In addition, we will determine if comic books are more effective for specific age groups of adolescents and youth compared to a text-only flyer. This work will advance Burkina Faso’s 2020–2024 Mental Health Strategic Plan and employ strategies suggested by the WHO Mental Health Action Plan 2013—2020. Increasing MHL has the potential to improve mental health outcomes as low levels of MHL have been linked to adverse mental health outcomes [37]. As randomized control trial studies on the effectiveness of comic books in impacting mental health literacy are few, this study will also add high quality research to future researchers who are considering this method of delivery.

Due to the nature of this light-touch intervention, its long-term effectiveness may be limited. In addition, the exposure to the light-touch intervention would benefit from repeated exposure over a period of time. By harnessing the potential of the comic book approach and incorporating lessons learned from this study, we aim to create a comprehensive comic intervention, including a digital format, in the future. Moreover, we will investigate the effect of our comic intervention on other countries part of the DASH study, including Ethiopia, Ghana, Nigeria, Uganda, South Africa, and Tanzania. Our study will provide valuable insights into innovative and engaging ways of communicating mental health information to adolescents and youth through NSHP delivery agents.

## Data Availability

No datasets were generated or analysed during the current study.
